### Burden of asthma

In 2004, about 300 million people worldwide were suffering from asthma (2). In the past decade, the prevalence of this chronic inflammatory disease has undoubtedly increased, and asthma could affect up to 400 million people by 2025 (2). In Canada, its prevalence is among the highest worldwide (2), affecting more than 10% of the population (2) and making it the most common respiratory disease in the country (1).

According to Canadian Guidelines, asthma control is defined by the frequency of daytime (<4 days/week) and night time symptoms (<1 night/week), by the capacity to perform normal physical activity, by the degree and frequency of exacerbations (mild, infrequent), and by the frequency of rescue medication needs (<4 doses/week). Moreover, there should be no absenteeism from school or work due to asthma. The values of forced expiratory volume in 1 second (FEV1, ≥90% personal best) and peak expiratory flow diurnal variation (PEF, <10%-15%) are also used to assess asthma control (3).

Asthma is unfortunately too often poorly controlled, resulting in a high socioeconomic burden (4). In Canada, hospital admissions account for the highest proportion of direct asthma-related costs from a societal perspective (5). Asthma indirect costs, such as work-loss days and premature deaths, are also important in the country (5).

Since the prevalence of asthma is increasing (2), and since costs of asthma increase with its severity and its poor management (6), developing new and efficient approaches to optimize asthma control is necessary.

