### Improving asthma control

Based on research information and effectiveness of treatment studies, Canadian Guidelines have suggested an optimal asthma management plan, which has been shown, when applied, to improve asthma control (1;7). However, many patients with asthma do not adhere to medical recommendations (4).

Adherence to treatments has first been defined as “the extent to which a person’s behaviour coincides with medical or health advice” (8). In addition, there are three components of adherence: acceptance, compliance and persistence (9). Compliance is “the extent to which a patient acts in accordance with prescribed interval and dose of a dosing regimen” (10) in order to optimize medication intake.

In asthma, both the insufficient use of controller medication and the overuse of rescue medication lead to uncontrolled asthma (11). Poor adherence with anti-inflammatory medication has indeed been shown in observational studies (12-14).

Poor adherence follows different patterns (15). Non-adherence may be unintentional, since patients may simply misunderstand their medication regimen. On the other hand, non-adherence may also be intentional, when patients worry about their medication intake and thereby decide not to fill their prescription or discontinue their treatment. In that case, poor compliance with asthma management plan is associated, among other factors, with patients' fears, misconceptions, and misunderstanding about treatments (4;16). In fact, communications are often suboptimal between patients and caregivers, who too often discuss neither patients' concerns about prescribed medication nor the pros and cons of the various recommendations (4). As a result of this, patients have to cope with a decisional conflict, which is defined as "the uncertainty about which course of action to take when choice among competing actions involves risk, loss, regret or challenge to personal life values" (17).

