### **Achieving asthma control**

In order to achieve asthma control, patients with asthma must avoid triggers and self-manage their symptoms, following a written action plan that physicians should have provided them with (3). Drug therapy is also an important part of asthma management, which highlights the

importance of physicians' adherence to asthma prescribing guidelines. Inhaled corticosteroids (ICS), as regular controller therapy, have been shown to effectively reduce asthma symptoms and improve, among other things, health-related quality of life (3). Long-acting beta2-agonists (LABAs), leukotriene receptor antagonists (LTRAs), and, in severe asthma, oral corticosteroids could be required as add-on therapy if asthma control is not achieved with the use of ICS alone (3). Treating acute asthma symptoms relies on reliever therapy, such as inhaled fast-acting beta2-agonists (FABAs). These, however, should be used at low-dose and low-frequency (3).

Several reasons may explain uncontrolled asthma. Physicians' non-adherence to asthma prescribing guidelines may be one of them. On the other hand, patients' lack of knowledge about the disease and its treatments may affect self-management (1). Moreover, inadequate environmental control at home, school, or work may lead to uncontrolled asthma, since atopy, tobacco smoke, and respiratory tract infections worsen symptoms (3). In addition, age is a predictor of the level of asthma control, since comorbidities increase with it (1). New evidences suggest that obesity may also be associated with uncontrolled asthma (1).

Other reasons may explain suboptimal asthma control. The level of asthma control may be over- or underestimated if an objective measurement of the patients' airflow obstruction is not undertaken (11). Moreover, many patients with asthma misunderstand their condition or the side-effects of pharmacotherapy (4), which highlights the need for educational interventions (11). Furthermore, both the insufficient use of controller medication and the overuse of reliever therapy, which underscore non-adherence, lead to uncontrolled asthma [1].

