### *Compliance with treatments (secondary outcome)*

Compliance with pharmacotherapy in the last week will be evaluated. An interview questionnaire based on the 2003 Asthma Consensus Conference guidelines (36) and adapted to the 2012 Asthma Consensus Conference guidelines (3) will be administered at baseline and after a 2-month follow-up. It has already been used to describe the appropriate use of asthma drugs among patients with moderate to severe asthma (19). The questionnaire is composed of a set of 11 hierarchical criteria; there were originally 12, but one of them is not relevant anymore. The set of criteria evaluates, in the last week, the use and the frequency of use of controller/rescue medication, and add-on therapy (if relevant). In order to be classified as compliant, patients need to meet all the 11 criteria (19), which set patients who are very compliant apart from others (37).

The questionnaire also allows compliance to maintenance/rescue/add-on medication to be expressed as a percent score ( $[\text{doses taken}/\text{doses prescribed}] \times 100$ ). In that case, a score that is  $\geq 80\%$  but  $\leq 100\%$  is indicative of compliance (38). The variable will nevertheless be analysed as a continuous one.

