### *Data analysis*

Descriptive analyses will be performed in order to describe the study population: continuous variables will be described as means or medians, depending on normality of distributions, and categorical variables as proportions.

Generalised linear models will be used to compare the intervention and control groups on the dependent variables (41). For asthma knowledge, decisional conflict, compliance with maintenance/rescue/add-on pharmacotherapy, and asthma control, a normal distribution and an identity link will be used, since all 4 variables are expressed as continuous ones. Assumptions of normality, and homoscedasticity will also be checked. A log transformation could be used to correct departure from normality, if relevant. For compliance with pharmacotherapy, a binomial distribution and a log link will be used as this variable is expressed as a binary one. In models, effects for group (intervention and control), time (baseline and 2-month follow-up) and group-by-time interaction will be included. The effect of the shared decision making aids on health outcomes will then be estimated by the interaction term between the group and time. Mean differences (continuous variables) and prevalence ratios (dichotomous variable) have been

chosen as effect measures. In addition, generalized estimating equations will be used in order to take repeated measures into account.

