**IG:** Intervention group (shared decision making) **CG:** Control group (usual care) **T1:** Baseline **T2:** 2-month follow-up

\* The effect of shared decision making aids on health outcomes will be estimated with their 95% confidence interval. The effect of the aids on asthma knowledge, decisional conflict, compliance with

controller/rescue/add-on pharmacotherapy, and asthma control will be expressed as means, since these variables are continuous. On the other hand, the effect of the aids on compliance with treatments (a binary variable) will be expressed as prevalence ratios. Both types of model will adjust for covariates, if a confounding variable results in a  $\geq 10\%$  change of the effect measure.

† P-value of the interaction term.

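### The rescue-medication compliance score falls as reliever use falls, so the low use the protocol aims for is scored as poor compliance

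*Protocol*

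**What the plan says.** The protocol section Compliance with treatments (secondary outcome) defines two measures. One is binary, based on 11 criteria. The other is a percentage: "The questionnaire also allows compliance to maintenance/rescue/add-on medication to be expressed as a percent score", calculated as doses taken over doses prescribed, times 100. A score from 80% to 100% "is indicative of compliance (38). The variable will nevertheless be analysed as a continuous one". Rescue drugs are named in this rule and not exempted from it.

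The Data analysis section carries the score into the models: for "compliance with maintenance/rescue/add-on pharmacotherapy, and asthma control, a normal distribution and an identity link will be used". The effect is the group-by-time interaction, reported as a mean difference. In Annexe 1, Table 1 lists the score as a continuous secondary outcome, and Tables 5 and 6 give rescue medication a separate row under compliance. The Table 6 footnote says that effects on compliance with "controller/rescue/add-on pharmacotherapy, and asthma control will be expressed as means, since these variables are continuous".

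On relievers themselves, the protocol takes this view:

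- Burden of asthma: control is defined in part "by the frequency of rescue medication needs (<4 doses/week").
- Improving asthma control: "both the insufficient use of controller medication and the overuse of rescue medication lead to uncontrolled asthma (11").
- Achieving asthma control: "Treating acute asthma symptoms relies on reliever therapy", and of the inhaled fast-acting drugs used for this, "These, however, should be used at low-dose and low-frequency (3").
- The section on achieving adherence through shared decision making aids reports reduced rescue use as a benefit in the earlier randomised trial of shared decision making in asthma.

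**The concern.** A ratio of doses taken to doses prescribed suits a drug taken on a schedule, where using less than prescribed is the failure to be detected. A reliever is taken when symptoms occur, so low use is what the protocol hopes to see. Under the shared formula and band, a patient who needs little or no reliever gets a low score and falls outside the compliant range.

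No section says which direction of the rescue score is favourable. The Hypothesis section ties better compliance to more maintenance drug use and does not mention relievers. The only stated guide to interpretation is the 80 to 100% band, which suggests that a score nearer 100% is better.

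At stake is the reading of the rescue row in Table 6. If the aids work along the hypothesised path, reliever need falls and asthma control improves. The rescue compliance mean would then fall in the aid arm, and a benefit could be reported as harm beside an improved control score. All three severity classes in Inclusion criteria include a short-acting reliever, so every patient with a countable reliever prescription is exposed to this.

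**Working it through.** The protocol gives no figure to reproduce here. The check applies its own formula at its own control limit.

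**Inputs**

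- Score = 100 × T / D, with T doses taken and D doses prescribed per week (Compliance with treatments).
- Compliant band: 80 to 100% (same section).
- Controlled asthma: fewer than 4 rescue doses a week, so at most T = 3 whole doses (Burden of asthma).
- D for relievers: not stated. Results are given first for general D, then for assumed values.

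**Results for any D**

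1. No reliever use: 100 × 0 / D = 0% for every D > 0.
2. Three doses reach the lower edge of the band when 300 / D ≥ 80, so D ≤ 300 / 80 = 3.75.
3. At D = 4 the score is 300 / 4 = 75%, already below the band. At D = 3 it is 100%. At D = 1 or 2 it exceeds 100%. Among whole numbers, only D = 3 puts three doses inside the band.
4. Each dose fewer per week changes the score by −100 / D, which is negative for every positive D.

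**Illustration with assumed D**

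| D per week (assumed) | Score at 3 doses | Points lost per dose fewer | Doses needed for 80–100% | Doses needed for 60% |
|---|---|---|---|---|
| 7 | 300/7 = 42.9% | 14.3 | 6–7 | 5 |
| 14 | 300/14 = 21.4% | 7.1 | 12–14 | 9 |
| 28 | 300/28 = 10.7% | 3.6 | 23–28 | 17 |

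In each row the use needed to count as compliant exceeds the limit of fewer than 4 doses a week. The last column takes the lowest of the sensitivity cut-offs in Data analysis (60 to 80%). The protocol does not say whether those cut-offs cover rescue drugs.

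As an example with assumed values, take a patient with D = 28 who goes from 24 to 3 doses a week. The score moves from 24/28 = 85.7% to 3/28 = 10.7%, a change of −75 points. The band turns from compliant to non-compliant as the patient comes within the control limit for reliever use.

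**The case against.** The strongest reply is that the denominator is unseen. The questionnaire is not reproduced, and its handling of as-needed drugs may differ from the plain formula. A purely as-needed prescription may give no countable D and so no score, which would be a different fault. This stands as a limit on size and reach: the illustrative figures rest on assumed D, and the problem applies only to patients with a countable prescription. It does not change the direction, which is the same for every positive D under the formula as written.

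A second reply is that little information is lost. With D fixed, the score is a rescaled dose count, rescue has its own row, and a reader who knows the protocol's stance on relievers could take a fall as benefit. The model does run. But the row is labelled compliance, no favourable direction is set, and choosing one after seeing the result is what a protocol should prevent. The 100% ceiling flags use above the prescribed amount, yet it does nothing for low use, and a mean difference cannot represent a two-sided band.

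Third, the band guides interpretation and is not the main analysis, and reliever use also enters the binary 11-criteria outcome, which is not shown to be affected. Both points are correct and limit the consequence. Neither repairs the continuous rescue row.

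Finally, a smaller change would do part of the work: keep the score, state that lower is favourable for rescue drugs, and exempt them from the 80% floor. That would settle the interpretation. It would still leave one dose fewer counting 14.3 points for a patient with D = 7 and 3.6 points for one with D = 28.

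**Conclusion.** The concern holds. The protocol applies a scheduled-drug formula and band to as-needed relievers and analyses the result as a continuous secondary outcome, against its own aim of low reliever use. A patient within the control limit of fewer than 4 doses a week reaches 80% only if 3.75 or fewer doses a week are prescribed, and every reduction in use lowers the score.

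The direction rests on two conditions: the formula is used as written, and the prescribed number does not change. The size depends on D, which the protocol does not give. The primary outcomes (knowledge and decisional conflict) are untouched, and the consequence is a risk of misreading one component of a secondary outcome in a pilot of 50 patients. The change should be made, but the trial does not depend on it.

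**What to change.** - In Compliance with treatments, Data analysis, Annexe 1 Tables 1, 5 and 6 and the Table 6 footnote, limit the percent score and the 80 to 100% band to regularly scheduled controller and add-on drugs.
- In Data analysis, state that the 60 to 80% cut-offs apply only to those drugs.
- For rescue medication, analyse the number of doses used in the last week, already collected as the numerator of the score, and state that lower is favourable. The proportion using fewer than 4 doses a week may be reported descriptively.
- Label the row as reliever use.

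The cost is wording in the protocol and tables, with no new data, visits or patients. The price is that the rescue row no longer measures compliance with a prescription and overlaps with asthma control, so its label must make that plain. Doses prescribed can still be recorded, so the later reanalysis of compliance foreseen under Perspectives remains possible.

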### *Asthma Control (Secondary Outcome)*

Asthma control will be quantified using the Asthma Control Scoring System (ACSS) (39), which is based on Canadian Asthma Consensus Guidelines. The ACSS will be administered at baseline and after a 2-month follow-up. Two types of parameters are assessed by the ACSS: the frequency of symptoms in the last week (clinical parameter) and the percentage of predicted value of FEV1 (physiological parameter). FEV1 will be measured according to the ATS criteria (40) and predicted values will be obtained from IUCPQ. Both clinical and physiological parameters will be expressed as a percent score and the mean of those scores will give the global asthma control score. If a score  $\geq 80\%$  is indicative of asthma control, the variable will however be analysed as a continuous one. Discriminative properties of the ACSS have been evaluated (30). The reliability of the instrument has been assessed through internal consistency testing and test-retest, and

has been shown to be acceptable. Moreover, correlation with other instruments evaluated construct validity, which has been shown to be good. Furthermore, evaluative properties of the ACSS were assessed: responsiveness indexes supported its sensitivity, which means that the instrument detects changes over time and between groups.

### *Asthma knowledge (covariate)*

Since the knowledge of asthma is also a predictor of decisional conflict and compliance with treatments, the values of the Asthma Knowledge Questionnaire (31), which will have been filled by patients at baseline, will be used. As a covariate, asthma knowledge will be modeled as a continuous variable.

### *Predictors of Asthma Control (Covariates)*

Age (in years) and body mass index for adults ( $\text{weight (kg)} / [\text{height (m)}]^2$  or  $\text{weight (lb)} / [\text{height (in)}]^2 \times 703$ ) will be assessed. In addition, inflammatory factors associated with asthma control will be measured. These factors are atopy (self-reported allergy; self-reported exposure to allergen), environmental triggers (smoking or exposure to second hand smoke), and respiratory tract infections in the last month. All those will be assessed through the IUCPQ Asthma Consultation Form. Covariate measurements will be undertaken at baseline. Questions regarding respiratory tract infections in the last month will also be asked after a 2-month follow-up. Factors associated with asthma control will be modeled as continuous or categorical variables.

### *Socio-demographic variables*

Socio-demographic variables (gender, level of education – using the categories of the Institut de la statistique du Québec) and the year of asthma diagnosis will be measured in order to better describe the study population.

### *Data analysis*

Descriptive analyses will be performed in order to describe the study population: continuous variables will be described as means or medians, depending on normality of distributions, and categorical variables as proportions.

Generalised linear models will be used to compare the intervention and control groups on the dependent variables (41). For asthma knowledge, decisional conflict, compliance with maintenance/rescue/add-on pharmacotherapy, and asthma control, a normal distribution and an identity link will be used, since all 4 variables are expressed as continuous ones. Assumptions of normality, and homoscedasticity will also be checked. A log transformation could be used to correct departure from normality, if relevant. For compliance with pharmacotherapy, a binomial distribution and a log link will be used as this variable is expressed as a binary one. In models, effects for group (intervention and control), time (baseline and 2-month follow-up) and group-by-time interaction will be included. The effect of the shared decision making aids on health outcomes will then be estimated by the interaction term between the group and time. Mean differences (continuous variables) and prevalence ratios (dichotomous variable) have been

chosen as effect measures. In addition, generalized estimating equations will be used in order to take repeated measures into account.

If covariates (asthma knowledge, age, body mass index, atopy, environmental triggers, and respiratory tract infections) are not distributed evenly between groups, we will adjust for them in analyses. Predictors of health outcomes will be incorporated into the model as confounders if they result in a >10% change in the effect measure, following a descending procedure. Exploratory subgroup analyses according to asthma severity will be conducted since pharmacotherapy and compliance with treatments are getting more complex with the severity of the disease. Statistical interaction of body mass index will also be exploratory assessed since this covariate is hypothesized to modify the effectiveness of intervention aiming at improving asthma control (42). In addition, exploratory statistical interaction of age, education and length of the patient's meeting with the asthma nurse will be evaluated since we hypothesize that the effect measure may vary according to the level of measurement of these variables. Regarding adherence to medication, sensitivity analyses will be carried out according to different cut-offs, that will range from 60 to 80% of inhaled prescribed doses.

SAS version 9.3 (SAS Institute Inc., Cary, USA) will be used to perform the statistical analyses, using PROC GENMOD. A 2-tailed *p*-value less than 0.05 will be considered indicative of statistical significance. Since the study is a pilot, power calculation will be made *a posteriori*. Alternatively, the study size is based on the number of patients that may realistically be recruited at the IUCPQ Research Center or Outpatient Asthma Clinic according to the timeframe. Nevertheless, sample size calculations will be made during the study, based on gathered data. If feasible, more patients may be enrolled in order to get sufficient statistical power.

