### ***Asthma knowledge questionnaire (primary outcome)***

Knowledge of asthma will be assessed by the Asthma Knowledge Questionnaire (31). The questionnaire will be filled by patients at baseline and after a 2-month follow-up. The French questionnaire comprises 37 items (true, false, don't know answers), evaluating 4 domains of asthma knowledge: biomedical, asthma severity, general knowledge and treatment (31). Developed in France, the original questionnaire had 38 items, but the eleventh has been withdrawn because it was not relevant in Quebec. The total knowledge score equals the good answers (rated 1) minus the wrong answers (rated -1). Don't know answers are rated 0. For each item, a negative score is indicative of asthma misunderstanding, a null score of a knowledge gap, and a positive score of gained asthma knowledge. The total knowledge score ranges from -37 to 37; thus, asthma knowledge will be modeled as a continuous variable. Psychometric properties of the questionnaire have been tested and showed good reliability and reproducibility (31).

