### *Decisional conflict (primary outcome)*

Decisional conflict will be assessed through a French version of OHRI Decisional Conflict Scale (18). The questionnaire will be filled at baseline and after a 2-month follow-up. Sixteen items evaluate 5 dimensions of decisional conflict (informed, values clarity, support, uncertainty, effective decision) using a Likert scale. Patients' responses range from 0 (strongly agree) to 4 (strongly disagree). Patients' responses are summed, divided by 16, and multiplied by 25. Consequently, the decisional conflict score ranges from 0 (low decisional conflict) to 100 (high decisional conflict). A score greater than 37.5 suggests that there is a meaningful decisional conflict, but a score that is less than 25 is not associated with it (33). The variable will nevertheless be analysed as a continuous one. The reliability of the OHRI Decisional Conflict Scale (English low literacy version) has been evaluated using a Cronbach's  $\alpha$ , which value was above the 0.7 threshold (34). Test-retest coefficient also supports its reliability (35). The scale has been shown responsive to change, because it is able to detect an effect size of 0.2 to 0.3 in studies that compare an intervention group to a control group (33).

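### The only remedy named for non-normality, a log transformation, is undefined for part of both primary outcome scales and does not estimate the mean difference the plan fixes

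*Protocol*

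**What the plan says.** The protocol's Data analysis section groups knowledge, decisional conflict, compliance with maintenance, rescue and add-on drugs, and asthma control as continuous, and specifies that "a normal distribution and an identity link will be used, since all 4 variables are expressed as continuous ones". It says the model assumptions will be checked and then gives the remedy: "A log transformation could be used to correct departure from normality, if relevant". No other remedy is named, no constant is to be added before taking logs, and no outcome is excluded. The same section names the mean difference as the effect measure for continuous outcomes, estimated by the group-by-time interaction with GEE in SAS PROC GENMOD. Table 6 of Annexe 1 agrees: all six continuous rows are normal with an identity link.

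The scales are defined elsewhere in the protocol:

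- Knowledge (primary): "The total knowledge score equals the good answers (rated 1) minus the wrong answers (rated -1"), with don't-know answers counted as 0, and "The total knowledge score ranges from -37 to 37".
- Decisional conflict (primary): "the decisional conflict score ranges from 0 (low decisional conflict) to 100 (high decisional conflict").
- Compliance (secondary): "The questionnaire also allows compliance to maintenance/rescue/add-on medication to be expressed as a percent score", namely doses taken over doses prescribed, times 100.

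**The concern.** A logarithm needs a strictly positive value. Both primary outcomes, and the percent compliance scores, can legitimately be 0, and knowledge can be negative. SAS returns missing for the log of zero or of a negative number, and PROC GENMOD omits records whose response is missing. The loss would therefore depend on the outcome itself: low knowledge scores, the best decisional conflict scores and the worst compliance scores. If the aids work, these values should be rarer or commoner in the intervention arm at 2 months, so the loss could differ by arm. The baseline and follow-up means would then rest partly on different patients.

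A second problem holds even where every value is positive. Taking logs changes what the interaction term estimates, so the result would no longer be the effect measure the section has fixed. The choice would be made after looking at the data.

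**Working it through.** **1. Reproduce the ranges.**

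- Knowledge: 37 items scored -1, 0 or +1 give totals from -37 to 37, as stated. That is 75 whole-number values, of which -37 to 0, or 38, have no logarithm.
- Decisional conflict: 16 items scored 0 to 4 sum to 0 to 64; sum / 16 × 25 gives 0 to 100, as stated. There are 65 attainable values in steps of 25/16 = 1.5625, and only 0 has no logarithm.
- Percent compliance: 0 doses taken / doses prescribed × 100 = 0, which has no logarithm.

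These are counts of possible scores, not of patients.

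**2. How many knowledge records might be affected?** The protocol gives no mean or SD for knowledge, so both are assumed. With a normal approximation and continuity correction, P(score ≤ 0) = Φ((0.5 - mean)/SD). For mean 10 and SD 8 this is Φ(-1.1875) = 0.1175, and 50 × 0.1175 = 5.9 records at one visit. Over SDs of 6 to 10:

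| Assumed mean | Expected records ≤ 0, of 50 at one visit |
|---|---|
| 5 | 11.3 to 16.3 |
| 10 | 2.8 to 8.6 |
| 15 | 0.4 to 3.7 |
| 20 | 0.03 to 1.3 |
| 25 | 0.0 to 0.4 |

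**3. How many decisional conflict zeros?** The Introduction reports that 72% of an earlier sample of 50 patients scored above 2. If those items ran from 1 to 5, a score of 2 corresponds to (2 - 1) × 25 = 25 on the 0 to 100 scale. With an assumed SD of 16, the mean that puts 72% above 25 is 25 + 0.583 × 16 = 34.3. With an assumed 8-point benefit, the other arm has mean 26.3. For a normal floored at 0:

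- control: Φ(-34.3/16) = 1.6%, and 25 × 0.016 = 0.4 patients;
- intervention: Φ(-26.3/16) = 5.0%, and 25 × 0.050 = 1.2 patients.

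If the items ran from 0 to 4, a score of 2 corresponds to 2 × 25 = 50. The means become 59.3 and 51.3, and both zero shares are below 0.1%. So zeros are few on either reading, although under the first they are about three times as frequent in the arm that benefits.

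**4. What the interaction estimates.** Write I and C for the arms and 1 and 2 for the visits.

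- Original scale: (mean I2 - mean I1) - (mean C2 - mean C1), a difference in score points.
- Log scale, exponentiated: (GM I2 / GM I1) / (GM C2 / GM C1), where GM is the geometric mean. This is a ratio.

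An offset does not restore the first quantity. The smallest whole-number offset covering the knowledge range is 38 (-37 + 38 = 1). With it, a gain from 5 to 10 counts as ln(48/43) = 0.110 and a gain from 20 to 25 as ln(63/58) = 0.083. The same 5 points carry different weights, and the weights depend on the constant chosen.

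**The case against.** The strongest reply is that the step is optional. The main specification is normal, identity link and mean difference. The log comes in only if a check fails and only where relevant, and the choice of outcome and offset could sit in a SAP that is not at hand. Harm requires a failed check, a decision to log one of these outcomes, no offset, and an analyst who accepts the missing values. All of this stands as a limit on severity. It does not repair the sentence: its condition concerns departure from normality, not whether a logarithm exists, and it names the log as the remedy for a group of outcomes that includes both primary ones.

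Stronger readings are tempting but not supported:

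- A reader might infer that the log fails for the knowledge score altogether. It fails only at 0 and below, and a total there needs at least as many wrong as right answers.
- A reader might infer that affected patients leave the analysis. With GEE on two visits the affected visit record is lost; the patient's other visit can still contribute.
- A reader might extend the problem to zeros on asthma control. That score averages a symptom score and an FEV1 score; no minimum is stated and a zero is not documented.
- A reader might add that compliance and control scores cluster near their top, so that a log would worsen the skew. The protocol gives no such distribution, and it describes asthma as often poorly controlled and maintenance drugs as underused.
- A reader might quote a percentage by which the decisional conflict effect shrinks once zeros are dropped. That figure depends heavily on the assumed mean, and it is an original-scale quantity that a log analysis would not report.

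**Conclusion.** The point holds in limited form. The one remedy the protocol names cannot be computed over the whole of either primary scale or for 0% compliance, and it does not give the protocol's own effect measure even where it can be computed. The domain problem follows from the scoring rules alone and needs no assumption. The number of records at risk does rest on assumptions: for knowledge, close to none of 50 if the mean is 20 or more with a small SD, several if it is near 10, and up to about a third if it is near 5; for decisional conflict, probably a patient or two at most. Any bias arises only if the option is used as written, and its size cannot be fixed from the protocol. Severity is minor to moderate.

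**What to change.** Delete the sentence offering a log transformation. State that the original-scale mean difference, the planned group-by-time contrast, is retained for all continuous outcomes whatever the normality check shows, with the robust (empirical) standard errors of the GEE already planned. If residuals are clearly non-normal, add as a named sensitivity analysis either a bootstrap interval, resampling patients with both visits together, or a permutation test of arm labels, in each case for that same contrast. This leaves the effect measure unchanged, uses every observed score and removes a data-dependent choice. The cost is one sentence of protocol text and a short extra analysis.
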